## Abstract

**Background::**

Rheumatoid arthritis (RA) is a chronic autoimmune disease characterized by swelling, pain, and synovial damage. Effective methods lack in the treatment of RA. A traditional prescription in use for thousands of years in China, Huangqi Guizhi Wuwutang granule (HGWG) is still chosen to relieve pain and prevent joint malformation in RA patients. However, no evidence-based medical research has been organized to assess the effectiveness and safety of HGWG for RA.

**Methods/design::**

We will conduct a multicenter, randomized, double-blind, placebo-controlled clinical trial to determine whether HGWG can relieve pain and protect joints. We will randomly divide 120 patients with active RA into 2 groups, treated for 12 weeks. Main measurement is the rate of ACR50 score (American College of Rheumatology) from the baseline to 12 weeks. Secondary measurements include rate of ACR20/70, change of Disease Activity Score (DAS) 28, Health Assessment Questionnaire-Disability Index (HAQ-DI), Patient Assessment of Arthritis Pain, Patient Global Assessment of Arthritis, and AIS score. The time points are set as baseline, 2 weeks, 4 weeks, 8 weeks, 12 weeks, 24 weeks, and 48 weeks. In addition, the rate of ACR50 from the baseline to 2 weeks, 4 weeks, 8 weeks, 24 weeks, and 48 weeks’ follow-up are also the secondary outcome measures.

**Discussion::**

The findings of this research will elucidate the efficacy and safety of HGWG and provide an alternative treatment for RA. In addition, our data will benefit the clinical decision-making on active RA and possibly be incorporated into future guidelines.

**Trial registration::**

ClinicalTrials.gov ID: NCT03593837.

## Introduction

1

Rheumatoid arthritis (RA), a chronic systemic inflammatory disease, mainly involves the synovium, leading to joint swelling, pain, bone erosion, and even deformity directly after over-accumulation of synovial fluid and fibrous tissues.^[1]^ Its overall prevalence is lower than 1%, and annual incidence is about 0.05%.^[2,3]^ Currently, the interventional efforts for RA focus on reducing the degree of disease activity, improving physical function and life quality, and restraining the development of complications.^[4]^ However, their outcomes are still unsatisfactory. So far, safe and effective anti-RA drugs have not yet been invented.^[5]^

As a complementary and alternative medicine (CAM), Chinese herbal medicine may have the potential of remitting RA symptoms or lowering disease activity.^[6,7]^ HGWG, a traditional Chinese medicinal formula with a history of thousands of years. To safeguard its quality for a longtime, Huangqi Guizhi Wuwutang decoction can be extracted into HGWG that has been used in our hospital for decades.

Although HGWG have been used clinically for many years, the efficacy and safety of HGWG still need evidence-based medical research. So, we plan to conduct a randomized, double-blind, placebo-controlled trial to confirm the efficacy and safety of HGWG in fighting against RA.

## Methods/design

2

### Study design

2.1

This study is a multicenter, randomized, double-blind, placebo-controlled clinical trial with 2 parallel arms (Fig. 1). The purpose of this study is to evaluate the efficacy and safety of HGWG in the treatment of RA. We will recruit 120 patients from 3 medical institutions in Shanghai, China: Longhua Hospital Affiliated with Shanghai University of Traditional Chinese Medicine, Shanghai Seventh People's Hospital, and Shanghai Guanghua Hospital of Integrated Traditional Chinese and Western Medicine. All patients will be randomly assigned to HGWG group (experimental group) and placebo (control) group.

**Figure 1 F1:**
[figure not shown]
Project overview. HGWG = Huangqi Guizhi Wuwutang granule, RA = rheumatoid arthritis.

Patients in the experimental group will be required to take in HGWG: twice a day, 1 package a time, after breakfast and dinner, for 12 weeks. Patients in the control group will use HGWG placebo in the same manner.

### Medication and administration

2.2

HGWG will be manufactured, packaged and labeled by a factory in Shanghai based on standards for good manufacturing practice. The procedures in the making of HGWG are listed in Table 1. The crude herbs include: *Astragalus membranaceus* (Huang Qi), 9 kg; *Cassia* twig (Gui Zhi), 9 kg; *Paeonia lactiflora*pall (Shao Yao), 9 kg; *Radix Glycyrrhizae* (Gan Cao), Ziziphus zizyphus (Da Zao), 18 kg. All materials will be supplied in 1 batch from Long Hua hospital and stored in a cool and dry place. The procedures in the making of HGWG are as follows:

1.three rounds of extractions – firstly, put the herbs listed above in a ceramic container, then add 1000 L of distilled water into the container to macerate the herbs for 1 hour, and then boil the mixture at 100°C for 1 hour for the first extraction; secondly, pour out the liquid extract, and add 1000 L of distilled water and boil it at 100°C for 1 hour; thirdly, extract after adding 500 L of distilled water and boiling for half an hour.2.concentration: concentrate the mixture of 3 extractions at 60°C (660 mm Hg) and spray-dry the mixture into powders. Then the powders are smashed and screened through a mesh size of 80. At last, the granules are packaged (4 g a bag) and stored in a clean room at 20°C and 50% humidity. HGWG placebo is made up of HGWG extraction (10%) and bitterant (90%). Pigment (such as lemon yellow, caramel pigment, and sunset yellow), edible lactose essence, and starch which makes the color, taste/smell, and shape are similar to HGWG.

**Table 1 T1:**
[figure not shown]
Components of HGWG.

Anti-rheumatic drugs (DMARDs), such as methotrexate (MTX) and sulfasalazine, may be used during the observation period. Patients’ original records are recorded. Non-steroidal anti-inflammatory drugs (NSAIDs) may be used to control patient's pain. The doctor responsible for the project will keep all medication records during the patients’ treatment. In addition, other conditions and treatments should be documented in the management manual. Both groups will have a 3-month treatment and a 9-month follow-up. At 7 time points (baseline, 2 weeks, 4 weeks, 8 weeks, 12 weeks, 24 weeks, and 48 weeks), visits will be scheduled for each patient. The plan is shown in Table 2.

**Table 2 T2:**
[figure not shown]
Schedule of enrollment and assessments.

### Ethical issues

2.3

The trial will be conducted in accordance with the *Declaration of Helsinki* and Ethical Guidelines for Clinical Research, and the trial protocol has been approved by the Research Ethical Committee of Longhua Hospital Affiliated with Shanghai University of Traditional Chinese Medicine, Shanghai, China, (approval number: 2018LCSY024), Guanghua Hospital of Integrated Traditional Chinese and Western Medicine (approval number: 2018-K-10), and Shanghai Seventh People's Hospital (approval number: 2018-IRBQY-014).

The physicians will invite the patient to participate in the trial, tell them in detail why we should take this trial and what kind of rights, obligations, and risks they will have if they participate the trials. And the care provider will give them a written informed consent. Only the patients who fully understand and sign the informed consent, can participant the trial.

Additionally, the personal information about the potential and enrolled participants will be collected to be used only in this trial, and we will not share or maintained the personal information when unnecessary.

### Participants

2.4

Recruitment notice for research participants is publicized on posters and websites at 3 hospitals (Longhua Hospital Affiliated with Shanghai University of Traditional Chinese Medicine, Shanghai Seventh People's Hospital, Shanghai Guanghua Hospital of Integrated Traditional Chinese and Western Medicine). All participants will receive informed consent before randomization.

### Sample size calculation

2.5

We calculated the sample size according to our primary study which conducted from January 2018 to October 2018 into the efficacy of the HGWG versus HGWG placebo, and we found that patients taking HGWG achieved 83.5% ACR50, whereas patients in the placebo group achieved 54.7% ACR50 response. Formula of sample size calculation is . In this formula, N1 and N2 are the number of HGWG and placebo group, *u*_α/2_ = 1.96 when type 1 error is 0.05; *u*_β_ = 1.282 when type II error is 0.1 in two-sided tests. is the mean of *p*_1_ and *p*_2_.^[8]^ It was estimated that approximately 50 participants per group were needed to achieve 90% power and a (2-sided) 5% significance level in detecting treatment differences. We estimate that 120 patients (60 in each group) will be enrolled to ensure that the results are statistically significant, considering a reduction rate of 20%.

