## Discussion

5

RA may lead to complications such as severe infection and malignant tumor.^[24–26]^ Inappropriately treating RA brings back with irreversible joint deformity and disability, which seriously affects the patients’ working ability and life quality of life. Doctors used DMARDs and MTX to treat RA patients with a good improvement. However, in MTX-resistant patients, the effective rate is only 25% to 40%.^[8,27–29]^ Therefore, it is urgent to develop new effective therapies. Chinese traditional medicine has accumulated rich clinical experience in the treatment of RA. HGWG has been used as a classic prescription of RA for thousands of years. Its effectiveness has already been experienced, but still needs to be scientifically confirmed with solid evidence.^[30,31]^ Therefore, we plan to carry out this multicenter randomized controlled clinical research.

To the best of our knowledge, this is a well-designed, randomized, controlled trial investigating the efficacy of the HGWG for the treatment of active RA. This study is built on our preliminary open trial with a small sample, as well as hundreds of years’ use of the HGWG in China for the treatment of RA. The findings of this research will elucidate the efficacy and safety of HGWG and provide an alternative treatment for RA. In addition, our data will benefit the clinical decision-making on active RA and possibly be incorporated into future guidelines.

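### The 20% loss allowance is computed the wrong way round: 60 per group leaves 48, below the protocol's own requirement of about 50, so the stated 90% power is not shown after loss

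*Protocol article*

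**What the plan says.** Section 2.5 of the protocol article (Sample size calculation) takes its planning rates from a 2018 study of HGWG against placebo: "patients taking HGWG achieved 83.5% ACR50" and "patients in the placebo group achieved 54.7% ACR50 response". It uses 1.96 for a two-sided 5% level and "1.282 when type II error is 0.1 in two-sided tests", in a formula that contains the mean of the two rates. It concludes that "approximately 50 participants per group were needed to achieve 90% power and a (2-sided) 5% significance level".

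The allowance for loss follows: "120 patients (60 in each group) will be enrolled to ensure that the results are statistically significant, considering a reduction rate of 20" per cent.

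Two other places bear on this. Section 4.6 (Statistical analysis) plans an intention-to-treat analysis with last observation carried forward for missing values. Section 5 (Discussion) says: "This study is built on our preliminary open trial with a small sample".

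**The concern.** The two steps of section 2.5 do not fit together. If about 50 per group are needed and a fifth of those enrolled are expected to be lost, the number enrolled must leave 50 after the loss. Sixty does not.

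The 90% power is the stated justification for 120 patients, so a reader will take it as the power that remains after the allowed loss. The sentence also says that this enrolment will ensure a significant result. No sample size can do that; it sets a probability of significance under an assumed difference.

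The whole calculation rests on the assumed difference of 83.5 − 54.7 = 28.8 percentage points. Section 2.5 presents its source as a comparison with placebo, while the Discussion describes a preliminary study that was open and small. The reader cannot tell whether these are one study or two.

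**Working it through.** **Inputs, all from section 2.5.** p1 = 0.835, p2 = 0.547, difference d = 0.288, mean rate p̄ = (0.835 + 0.547)/2 = 0.691, multipliers 1.96 and 1.282, loss 20%. Allocation is 1:1 (section 3.4).

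Intermediate values: 2p̄(1 − p̄) = 2 × 0.691 × 0.309 = 0.4270; p1(1 − p1) + p2(1 − p2) = 0.1378 + 0.2478 = 0.3856; d² = 0.0829.

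**Step 1: the stated figure of about 50.** The equation is missing from the text available to me, so I tried the standard forms.

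- Pooled variance under the null, unpooled under the alternative (the usual form with the mean rate): [1.96√0.4270 + 1.282√0.3856]²/0.0829 = 52.0. Unrounded normal quantiles give 51.99, so 52.
- Pooled variance in both terms: (1.96 + 1.282)² × 0.4270/0.0829 = 54.1, so 55.
- Unpooled variance, which does not use the mean rate: (1.96 + 1.282)² × 0.3856/0.0829 = 48.9, so 49.

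The usual form is within two patients of 50. I treat the stated figure as reproduced.

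**Step 2: the allowance for loss.**

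- As done: 50 × 1.2 = 60. Check: 60 × 0.8 = 48, which is below 50.
- As needed: 50/0.8 = 62.5, so 63 per group, 126 in total. Check: 63 × 0.8 = 50.4.

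This step needs no assumption about the missing equation.

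**Step 3: power for 83.5% against 54.7%, two-sided 5%.** The normal-approximation formulas, with Φ the standard normal distribution function, are:

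- Pooled null, unpooled alternative: Φ[(d√n − 1.96√0.4270)/√0.3856]. At n = 48: (1.995 − 1.281)/0.621 = 1.151, giving 87.5%.
- Pooled in both terms: Φ[d√n/√0.4270 − 1.96]. At n = 48: 3.053 − 1.96 = 1.093, giving 86.3%.
- Unpooled: Φ[d√n/√0.3856 − 1.96]. At n = 48: 3.213 − 1.96 = 1.253, giving 89.5%.

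The exact column sums the binomial probabilities of all outcomes that the uncorrected chi-square test declares significant.

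| Analysed per group | Pooled null, unpooled alternative | Pooled in both | Unpooled | Exact, chi-square |
|---|---|---|---|---|
| 48 (60 less 20%) | 87.5% | 86.3% | 89.5% | 88.4% |
| 50 (stated need) | 88.8% | 87.6% | 90.7% | 89.2% |
| 60 (all randomised) | 93.7% | 92.7% | 94.9% | 94.2% |

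At 48 per group every method falls below 90%. At 60 per group every method exceeds it, provided the planning rates hold for everyone analysed.

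**The case against.** The strongest reply is that section 4.6 does not drop patients. Under intention-to-treat with last observation carried forward, up to 60 per group stay in the comparison, and power is then about 93–94% if the assumed rates hold. This stands, and it makes the shortfall conditional. It does not repair section 2.5, which sizes the trial as if a fifth were lost. Nor does it settle the power: an early value carried forward for a 50% improvement criterion may not match the 12-week response, and the article gives nothing from which to estimate that dilution.

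The effect is also small. Against the article's own target, the slip costs two evaluable patients per group, and power moves from 88.8% to 87.5% in the usual form. The article also does not say whether the 20% is expected by week 12 or by week 48; if by week 48, fewer would be lost at the primary time point.

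A reader might infer more than the article supports:

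- *That the figure of about 50 is itself wrong.* The usual form with the mean rate gives 52, a fair reading of approximately 50. A figure of 55 requires pooled variance in both terms, which cannot be confirmed without the equation.
- *That power is only 72–74%.* This follows if the 20% who drop out all count as non-responders among 60 per group (0.8 × 83.5% = 66.8% against 0.8 × 54.7% = 43.8%). Section 4.6 uses no such rule; under last observation carried forward, a patient who leaves while responding remains a responder.
- *That the planning difference is inflated because the preliminary study was open.* The article never says that the study in section 2.5 and the one in the Discussion are the same. Read as simple proportions, 83.5% needs at least 79 patients (66/79) and 54.7% at least 53 (29/53), which sits oddly with a small sample. That is a reason to ask, and it shows no wrong number.

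**Conclusion.** Section 2.5 contradicts itself: its enrolment does not deliver its own requirement after its own allowance for loss. With 48 evaluable per group, power for 83.5% against 54.7% is about 86–88% by the forms that use the mean rate and by exact chi-square, or 89.5% with unpooled variance, where the article states 90%.

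It would go too far to say that the trial lacks 90% power outright. The shortfall rests on two assumptions: that the full 20% are lost before the 12-week assessment, and that they leave the analysis. Under the planned analysis of all 60 per group, power is about 93–94% if the assumed rates hold, and lower by an unknown amount if carried-forward values narrow the difference.

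The claim that enrolment will ensure significance is wrong whichever analysis is used. The source of the planning rates needs clarifying, but it is not shown to be in error. Overall severity is minor to moderate.

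**What to change.** Keep 120 patients and change the text of section 2.5.

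1. Replace the statement on loss and power with, for example: *With 60 randomised per group and 20% loss, 48 evaluable per group give about 86–88% power for 83.5% against 54.7%. If all 60 per group are analysed under intention-to-treat with last observation carried forward and the assumed rates hold, power is about 93–94%, and less if carried-forward values dilute the difference.*
2. Delete the clause saying that this enrolment will ensure statistically significant results.
3. Reconcile section 2.5 with the Discussion: say whether the HGWG versus placebo study and the preliminary open trial are the same, and which of them supplied the planning rates.

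The cost is rewording, and one of the two stated powers becomes slightly less favourable. No extra patients are needed. If the sponsor prefers to keep the statement that about 50 per group remain after a 20% loss, the enrolment consistent with it is 63 per group (126 in total), six more than planned.

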## Criteria

3

### Inclusion criteria

3.1

Participants meeting the following requirement will be included.

Diagnosed with RA according to the diagnostic criteria developed by the American College of Rheumatology in 1987.DAS28 score of 2.6 to 5.1.Aged 18 to 70.Signing informed consent and ensuring test compliance.Women of childbearing age must undergo testing and have no pregnancy plan throughout the trial.Having no history of combined disease and active tuberculosis.

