### Exclusion criteria

3.2

Having any concurrent rheumatic disease, such as systemic lupus erythematosus, Sjogren's syndrome, or severe osteoarthritis.Having tumor and cancer.Having a history of serious allergic reactions.Pregnant or lactating women and women of childbearing age who do not have an effective contraceptive method.Having cardiac, hematologic, respiratory, neurological, endocrine, renal, hepatic, gastrointestinal, or psychotic disease.Having infectious diseases.Showing poor compliance, and unwillingness to be followed-up.Showing alcoholism or drug dependency.

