### Interventions

3.3

Experimental group (HGWG group): Patients are given HGWG (orally twice a day for 12 weeks and instructed to dissolve one package (4 g) with hot water (200 mg). Control group: HGWG placebo will be used in the same way.

Supportive therapy of two groups:

1.DMARDs can be used during the observation period, such as MTX and sulfasalazine (the original dose will be maintained);2.According to the patient's pain severity, NSAIDs can be added;3.Patients should provide a detailed list of drugs used during follow-up and observation period. Researchers must record the name of the drugs, dosage, frequency, and duration.

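### Entry sets no period of unchanged DMARD treatment before baseline, so a recent starter's DMARD response counts towards week-12 ACR50 in both arms and dilutes the contrast

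*Protocol article*

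**What the plan says.** Section 3.1 introduces its entry list with "Participants meeting the following requirement will be included". The disease-related entry criteria in Section 3.1 are a diagnosis, "Diagnosed with RA according to the diagnostic criteria developed by the American College of Rheumatology in 1987", and an activity range, "DAS28 score of 2.6 to 5.1". The other four concern age, consent and compliance, pregnancy, and absence of combined disease or active tuberculosis. The exclusions in Section 3.2 cover comorbidity, allergy, pregnancy, infection, dependency and items such as "Showing poor compliance, and unwillingness to be followed-up". None mentions when a DMARD was started or last changed.

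Background treatment appears in two places. Section 3.3 says "DMARDs can be used during the observation period, such as MTX and sulfasalazine (the original dose will be maintained". Section 2.2 also permits DMARDs during observation, but says nothing about holding the dose. Both sections require medication to be recorded.

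The primary endpoint (Section 4.1) is ACR50 response from baseline to 12 weeks. Randomization (Section 3.4) is 1:1 and stratified by centre only. The planning rates (Section 2.5) are 83.5% ACR50 on HGWG, while "patients in the placebo group achieved 54.7% ACR50 response".

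**The concern.** Holding a dose after entry is not the same as requiring that it was already settled at entry. Two patients with the same baseline DAS28 are treated alike by the criteria: one on a long-standing DMARD with residual activity, and one who started the same drug the week before. For the second, keeping the dose constant for 12 weeks means the drug's own onset takes place during the primary endpoint window. The Discussion itself says that patients treated with DMARDs and methotrexate improve well.

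Such a patient may reach ACR50 whichever arm he or she is in. That leaves HGWG less to add, so the difference between the arms shrinks and power falls. A null result would be harder to read, because a real effect could have been masked by background improvement that the entry criteria could have limited.

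**Working it through.** **Text check.** Six inclusion criteria and the exclusion list were read against Sections 2.2, 3.3 and 3.4. No passage sets a minimum time on a DMARD or an unchanged dose before baseline, and DMARD use is not a stratification factor. Eligibility is protocol content; an analysis plan could not supply it later.

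**Inputs from the documents (Section 2.5).** p1 = 0.835, p2 = 0.547, difference 0.288, two-sided 5%, 90% power, about 50 per group, 60 per group enrolled.

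**The plan's own figure.** With the pooled-variance formula,

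n = [1.96·√(2·p̄(1−p̄)) + 1.282·√(p1(1−p1) + p2(1−p2))]² / (p1−p2)²

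and p̄ = 0.691, n = (1.96·0.6535 + 1.282·0.6209)² / 0.0829 = 52 per group. The stated 50 is reproduced closely enough.

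**Power at the planning rates, n = 60 per group.**

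power = Φ{[d − 1.96·√(2p̄(1−p̄)/n)] / √[(p1(1−p1) + p2(1−p2))/n]} = Φ[(0.288 − 0.1653)/0.0802] = 93.7%.

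**Assumed inputs, not in the documents.** A share f of patients are recent starters who reach ACR50 at rate r on placebo. I take f = 10 or 20% and r = 70 or 80%; the rest follow the planning rates. The placebo rate becomes b = (1−f)·0.547 + f·r. Two assumptions about HGWG bracket the effect:

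- *Model A:* HGWG converts the same fraction of would-be non-responders in everyone: k = 0.288/0.453 = 0.636, HGWG rate = b + k(1−b).
- *Model B:* HGWG adds nothing in starters: HGWG rate = (1−f)·0.835 + f·r.

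| f | r | Placebo rate | A: difference | A: power | B: difference | B: power |
|---|---|---|---|---|---|---|
| 0% | – | 54.7% | 28.8 | 93.7% | 28.8 | 93.7% |
| 10% | 70% | 56.2% | 27.8 | 92.5% | 25.9 | 87.7% |
| 10% | 80% | 57.2% | 27.2 | 91.6% | 25.9 | 88.4% |
| 20% | 70% | 57.8% | 26.9 | 91.1% | 23.0 | 78.8% |
| 20% | 80% | 59.8% | 25.6 | 89.1% | 23.0 | 80.4% |

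Example (A, f = 20%, r = 80%): b = 0.8·0.547 + 0.2·0.8 = 0.5976; HGWG rate = 0.5976 + 0.636·0.4024 = 0.8534; power = Φ[(0.2558 − 0.1597)/0.0781] = 89.1%.

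**Noise from chance imbalance.** With f = 20% and 60 per arm, the standard deviation of the between-arm difference in the share of starters is √(2·0.2·0.8/60) = 7.3 points. Multiplied by the assumed excess response of starters (0.70 − 0.547 = 0.153, or 0.80 − 0.547 = 0.253), that shifts the ACR50 difference by about 1.1 to 1.8 points, against a standard error of about 8 points. It is small, and the test's error rate already allows for it.

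**The case against.** The strongest reply is that the trial is randomized, double-blind and placebo-controlled, so DMARD onset falls equally on both arms in expectation. That stands. A reader might infer that recent starters would inflate the apparent effect of HGWG; nothing in the design supports that. The expected direction is dilution.

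Second, the 54.7% comes from an earlier HGWG-versus-placebo study whose rules on background DMARDs are not shown. If it admitted the same mix, recent starters are already in that rate and the losses above count them twice. This also stands.

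Third, a much larger power loss can be produced. Under Model A, a placebo rate of 70% gives a 19-point difference and 74% power. But reaching 70% needs every patient to be a starter if starters respond at 70%, or (0.70 − 0.547)/(0.80 − 0.547) = 60% of patients if they respond at 80%. Nothing in the article suggests such shares.

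Fourth, a reader might infer from the Discussion's remark, "in MTX-resistant patients, the effective rate is only 25% to 40", that the trial is meant for methotrexate-resistant patients and fails to select them. The abstract, the introduction and Section 2.1 argue from RA in general; this is one sentence, no result is claimed for that group, and such patients are not excluded. Nor can the 25 to 40% be set against the planned 54.7%, since its response measure is not stated. Likewise, "provide an alternative treatment for RA" might be read as a claim of superiority to DMARDs, but Sections 2.2 and 3.3 state openly that DMARDs and NSAIDs are background in both arms. Admitting patients with mixed background therapy is a legitimate pragmatic choice.

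What survives all this is narrow: allowing mixed background therapy does not require allowing background therapy that has only just been started or changed.

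**Conclusion.** The gap is real. The protocol holds a DMARD dose after entry without requiring that it was unchanged before, so recent starters are eligible and their DMARD response counts as ACR50 response at week 12 in both arms. The consequence is dilution and a little extra noise, not bias towards HGWG.

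The size is moderate and uncertain. At 60 per group, power falls from 94% to about 89 to 92% under Model A and about 79 to 88% under Model B. These ranges rest on an assumed 10 to 20% share of starters, on a 70 to 80% response among them, and on the 54.7% not already including them; if it does, the loss is smaller. The documents do not support going further to a biased comparison, to power near 74%, or to a trial that has failed a methotrexate-resistant target population.

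**What to change.** - Add to Section 3.1 that any background DMARD has been unchanged for a minimum period before baseline. The sponsor sets the length.
- Reconcile this with Sections 2.2 and 3.3, so that all three say the same about background DMARDs; at present only Section 3.3 mentions maintaining the dose.
- Adjust the week-12 ACR50 comparison for baseline DMARD use. The medication records required in Sections 2.2 and 3.3 already capture this, so no new data collection is needed.

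The cost is one entry criterion and one covariate. The downside is that recent starters must wait before they can enter, which slows recruitment slightly.

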### Primary outcome measure

4.1

ACR50 from baseline to 12 weeks after treatment will be compared. ACR50 is a standard to describe RA symptoms.^[9]^ ACR 50 is met when the number of tender joints reduces by ≥50%, the number of swollen joints by ≥50%, and at least 3 of the following 5 indexes improves by ≥50%:

Patient's assessment on arthritis pain using a Visual Analogue Scale (VAS) of 0 to 100 mmPatient's global assessment of disease activity using VAS scale (0–10)Patient's assessment of physical function and disability HAQ-DIErythrocyte sedimentation rate (ESR)C-reactive Protein (CRP) level

Similarly, ACR20 is met when ≥20% is achieved in the reduction of tender joint number, swollen joint number, and indexes of 3 of the 5 other measurements.^[10]^

ACR scale has been accepted as the efficacy benchmark in RA clinical trials and has greater discriminant capacity to distinguish patients on active treatment from placebo control.^[9,11,12]^ Here we choose ACR50 as the primary index for that ACR50 can provide more useful information than ACR 20/70.^[13,14]^

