### Secondary measurements

4.2

The secondary outcomes will be to compare the rates of change in the ACR20/70, DAS28, HAQ-DI, Patient Assessment of Arthritis Pain, Patient Global Assessment of Arthritis, and AIS score from baseline to 2 weeks, 4 weeks, 8 weeks, 12 weeks, 24 weeks’ and 48 weeks’ follow-up. The rate of change in the ACR50 from the baseline to 2 weeks, 2 weeks, 4 weeks, 8 weeks, 12 weeks, 24 weeks’ and 48 weeks’ follow-up are also secondary outcome measures. Additionally, the change in score on the 36-item Short-Form Health Survey Questionnaire (SF-36) from baseline to 4 weeks, 8 weeks, 24 weeks, and 48 weeks is also calculated.

The DAS28 is an index calculating the number of painful and swollen joints (28 joints, i.e. shoulders, elbows, wrists, metacarpophalangeal and proximal interphalangeal joints, and knees), ESR and the score of global assessment.^[15]^ The formula of DAS 28 is 0.56 × √(28 painful joint count) + 0.28 × √(28 swollen joint count) + 0.70 × (ln ESR) + 0.014 × GH. ESR refers to ESR. GH is the patient's general health visual analog scale (0–10 mm).^[16–18]^

HAQ-DI is a subscale of ACR 20/50/70 that reports biochemical and physical conditions. It has been widely used in RA clinical trials to assess disease activity and patient disability.^[19]^ The HAQ-DI measure shave eight dimensions of functional activity: pruning, dressing, rising, eating, walking, personal hygiene, reach, grip, and other routine activities. Each item has 4 degrees ranging from 0 to 3. “0” refers to “no functional difficulty”, “1” to a bit of functional difficulty, “2” to very much functional difficulty, and “3” to no ability to work. HAQ-DI score 0 to 1 means mild to moderate functional difficulty; 1 to 2 means moderate to severe disability; and 2 to 3 means generally severe disability.^[20]^

People with RA often have sleep disorders that worsen as RA deteriorates.^[10,21]^ The Athens Insomnia Scale (AIS) can help patients quantitatively self-evaluate sleep disorders with a psychometric instrument that includes eight indicators for sleep induction, awakenings during the night, final awakening, total sleep duration, sleep quality during the night, wellbeing during the night, functioning capacity during the day time, and sleepiness during the day time. The score for each indicator ranges from 0 to 3, and the total score is 24 points. The higher the score, the worse the sleep quality, and vice versa.^[22]^

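### The printed entry criteria do not guarantee a tender and a swollen joint at baseline, although ACR50 needs both counts to halve

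*Protocol article*

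**What the plan says.** Section 3.1 (Inclusion criteria) has two items that bear on disease status. The first is the diagnosis: "Diagnosed with RA according to the diagnostic criteria developed by the American College of Rheumatology in 1987". The second is current activity: "DAS28 score of 2.6 to 5.1". The other inclusion items concern age, consent, pregnancy and other disease. The exclusion list in 3.2 says nothing about joint counts. The abstract describes the population as active: "We will randomly divide 120 patients with active RA into 2 groups". No criterion turns that word into a number of joints.

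Section 4.1 (Primary outcome measure) defines the endpoint: "ACR 50 is met when the number of tender joints reduces by ≥50%, the number of swollen joints by ≥50" per cent, and at least 3 of 5 further indexes (pain, patient global, HAQ-DI, ESR, CRP) must also improve by at least 50%. Both joint conditions are compulsory.

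Section 4.2 (Secondary measurements) gives the DAS28 formula as "0.56 × √(28 painful joint count) + 0.28 × √(28 swollen joint count) + 0.70 × (ln ESR) + 0.014 × GH". GH is described there as the "general health visual analog scale (0–10 mm"). Section 4.6 states an intention-to-treat approach, with last observation carried forward for missing values.

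**The concern.** The entry rule and the primary endpoint rest on different quantities. DAS28 is a sum, so a high ESR or a high tender count can make up for a swollen count of zero. ACR50 allows no such trade: each joint count must fall by at least half of its baseline value. From a baseline of zero that fraction does not exist.

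If such patients are enrolled, the trial has randomised people whose primary outcome is settled by a convention. Counting the undefined component as not improved makes them non-responders whatever treatment they receive, which pulls the two rates together. Counting it as met leaves them to be judged on a weaker endpoint than everyone else. Carrying the last observation forward does not help, because the value is undefined rather than missing.

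**Working it through.** **Inputs.** Entry range 2.6 to 5.1 (3.1). DAS28 formula and GH scale of 0 to 10 (4.2). ACR50 definition (4.1). Planning rates 83.5% and 54.7%, two-sided 5%, 90% power, about 50 per group, 60 per group enrolled (2.5).

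**Step 1. Reproduce the plan's own figure.** With p1 = 0.835, p2 = 0.547, mean p = 0.691 and difference d = 0.288, the pooled-variance formula is

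n = [1.96 × √(2 × 0.691 × 0.309) + 1.282 × √(0.835 × 0.165 + 0.547 × 0.453)]² / 0.288²

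= [1.96 × 0.6535 + 1.282 × 0.6209]² / 0.0829 = 52 per group.

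The unpooled form gives 49. Both agree with about 50, so the sample size is not at issue here.

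**Step 2. Can a patient with a zero count enter?** Using the 4.2 formula:

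- 4 tender, 0 swollen, ESR 10, GH 5: 0.56 × 2 + 0 + 0.70 × 2.303 + 0.014 × 5 = 1.12 + 1.61 + 0.07 = 2.80. Eligible.
- 0 tender, 0 swollen, ESR 40, GH 5: 0.70 × 3.689 + 0.07 = 2.58 + 0.07 = 2.65. Eligible.

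With no affected joint and GH 5, the lower limit is reached at ESR = exp[(2.6 − 0.07)/0.70] = 37.1. With 4 tender and 0 swollen joints it is reached at ESR = exp[(2.6 − 1.12 − 0.07)/0.70] = 7.5.

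A zero swollen count is the easier case. At ESR 20 and GH 5, the terms other than joints give 0.70 × 2.996 + 0.07 = 2.17. One tender joint brings this to 2.73, and 27 tender joints bring it to 5.08. So every tender count from 1 to 27 qualifies with no swollen joint.

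**Step 3. Does the GH scale matter?** If GH were on 0 to 100 (an assumption), no affected joint with ESR 20 and GH 50 gives 2.10 + 0.70 = 2.80, which is also eligible. The result holds on either scale.

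**Step 4. What happens to the endpoint?** The relative reduction is (baseline − week 12)/baseline. With a baseline of 0 and a week 12 count of 0, it is 0/0. In the first example this affects the swollen component, in the second both.

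**Step 5. Illustrative size.** Let a share f of each arm have an undefined joint component and score as non-responders, and suppose that the planning rates contain no such patients. Both rates are then multiplied by (1 − f), and

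power = Φ{[d√60 − 1.96 × √(2 × mean p × (1 − mean p))] / √(p1(1 − p1) + p2(1 − p2))}.

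| f | rates | difference | power at 60 per arm |
|---|---|---|---|
| 0 | 83.5% v 54.7% | 28.8 points | 93.7% |
| 5% | 79.3% v 52.0% | 27.4 points | 89% |
| 10% | 75.2% v 49.2% | 25.9 points | 84% |

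The documents give no value for f.

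**The case against.** **The entry rule is more than a DAS28 range.** A 1987 ACR diagnosis is also required and the population is called active. That is true, but the text attaches no current joint count to either, so the gap remains.

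**Zero among 28 joints need not be zero for ACR50.** This stands in part. The article does not say which joint set ACR50 uses. A reader might infer that ACR50 is never computable for these patients. That is too strong: it is undefined only if the count is also zero on the set actually used. No text requires a non-zero count on any set.

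**One-joint baselines.** A reader might go further and argue that a miscounted single joint creates ACR50 responses, and that this explains the 54.7% placebo rate. The documents do not support it. A response also needs 3 of 5 other indexes to improve by at least 50%, so a joint count alone cannot produce one. No baseline joint counts are reported for the earlier study.

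**The power figures.** A reader might take 84% as the expected power. It is not. The 5% and 10% shares have no source in the article. The planning rates come from an earlier study whose entry rules are not described. If it enrolled similar patients, they are already in the 83.5% and 54.7%, and no further loss applies. This objection stands in full.

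**Scoring a zero baseline belongs in the analysis plan.** Also accepted, and its absence here is not part of this point. An analysis plan can choose a convention, but it cannot change who is enrolled.

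**Conclusion.** The mismatch holds and follows from the article's own formula: sections 3.1 and 3.2 admit patients whose baseline tender or swollen count is zero, while section 4.1 needs a proportional fall in both. It rests on the criteria as printed and on ACR50 being counted on a joint set where these patients also have zero.

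The consequence is less certain than the mismatch. Such patients cannot show benefit on the undefined component. Scored as non-responders they dilute the difference. Scored as having met the component they are judged on the remaining conditions only, which is a different endpoint. How much this matters depends on a share that the article does not give, so the figures of about 89% and 84% show sensitivity and are no forecast. The point is worth correcting because the correction is small. It does not show that the trial is underpowered.

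**What to change.** Add to section 3.1 a requirement of at least one tender and at least one swollen joint at baseline, and name the joint set, which should be the one used for ACR50. One of each is the smallest floor that makes both joint components exist for every randomised patient. Nothing in the documents supports a particular higher threshold.

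The counts are already needed for DAS28 and ACR50, so no new assessment is added, and the sample-size inputs in 2.5 stay as they are. The cost is an eligibility amendment, best made before the first patient is enrolled. A few low-activity patients would become ineligible and recruitment may be slightly slower. The article gives no data from which to estimate how many.
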